### Outcome measures

Clinical examinations of outcome measures are highlighted in Table 2, are collected at baseline, end of treatment (6 weeks), and then 6, 12 and 24 weeks after the end of treatment. These are performed by clinicians with appropriate experience in their application. The primary outcome measure is the.

**Table 2 Tab2:** Study Outcome Measures

**Primary outcome measure** (End of treatment – 6 weeks)	Mean NRS for 7 days.
**Secondary outcome measures**	MAS
	MRC
	Leeds Arm Spasticity Impact Scale
	ARAT
	EQoL 5D-5 L
	SQoL − 6

averaged 7-day NRS-S. This is a simple patient reported level of elbow spasticity where 0 = no spasticity and 10 = worst possible spasticity. This is recorded daily either on paper report forms or digitally according to patient preference. Its validity and reliability in stroke is established as is the minimally important clinical difference (MCID) [18]. Through co-design we have adapted the NRS-S to enable easier completion amongst those with cognitive impairment and aphasia (Fig. 2). The MCID for the NRS-S is a change of ≥ 18% (i.e. 2 points) from baseline to follow up assessment. ^17^ The primary endpoint for this study is the proportion of participants experiencing this MCID improvement in each group. Averaged 7-day NRS-S is calculated at baseline, end of intervention (6 weeks), and then at 6 weeks, 12 weeks and 24 weeks after the end of intervention (Fig. 3).

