### Statistical analysis and sample size

Study analysis will be conducted on an intention to treat basis. Baseline characteristics will be presented by treatment group. Summary statistics for each of the endpoints will be reported at each available time point (baseline, EOT, and 6, 12 and 24 weeks after end of treatment). Results will be reported with confidence interval where relevant, for example, in reporting the average difference between treatments in the secondary endpoints. We previously carried out a community-based study using the NRS-S as an outcome measure [16]. Analysis of data from the study was used for the sample size calculation. A change in average NRS-S of 18% from baseline to follow-up time point (MCID) is considered a success. The proportion of successes will be compared between groups (pairwise).

A parallel gatekeeper design has been developed such that the first two significance tests share the total *p*-value equally (each tested at 0.025 level). This will be split equally between the first primary objective (SHAPES vs. usual care, and TENS vs. usual care at EOT (6 weeks) using 2.5% significance each). If one or both of these tests are significant then the *p*-value will be reutilised for testing the second primary objective (SHAPES vs. TENS at EOT and 6 weeks after EOT). This will utilise Chi-squared test (or an exact test if required). Between group efficacy at follow up timepoints (3 and 6 month) will also utilise a continuity corrected Chi-squared test.

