We calculated the sample size using data from our previous study [15]. The sample size calculation for a two group t-test for equal means showed that to conduct a three arm randomized control trial of SHAPES, TENS and ‘usual care’ control, we would need 66 subjects per group (total 198 participants) to have 90% power to demonstrate a MCID reduction of 18% in NRS at the 1% significance level to allow for multiple testing. In our feasibility study 67% of participants showed good adherence with the intervention and 73% with recording of NRS. We will recruit a total of 297 patients with PSES to the study who are being randomised to one of the 3 arms. We aim to achieve a minimum of 66 participants to adhere to and complete the protocol in each group with good adherence to the intervention schedule and a minimum of 4 of 7 daily NRS-S recording. This will be known as the Per Protocol Set (PPS). Sensitivity analyses will be conducted to investigate the impact of missing or incomplete data, non-compliance, and spasticity severity. The sample size calculation was done in R using simulations.

Analysis of other secondary objectives (ARAT, MAS, MRC, LASIS, EQ-5D, SQoL-6D) will use repeated measures analysis with treatment group and timepoint as factors, baseline as a covariate and subject as a random effect to investigate the within-participant change in each outcome over time and to see if there is a treatment effect. As some of these outcomes are ordinal, it may not be possible to satisfy the conditions of a repeated measures ANOVA thus Friedman test may be used instead with pairwise Wilcoxon Signed Rank tests for any post-hoc analysis requirements. Since these analyses are exploratory, no adjustment for multiplicity will be made – nor will significant conclusions be drawn.

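### The stated 90% power belongs to a t-test on mean NRS-S at 1%, not to the planned chi-squared comparison of responder proportions at 2.5%

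*Protocol article*

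**What the plan says.** The sample-size paragraph appears in the protocol article under Participants and again under Statistical analysis and sample size.

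- Sizing test: "The sample size calculation for a two group t-test for equal means".
- Sizing result: "we would need 66 subjects per group (total 198 participants".
- Sizing power and level: "to have 90% power to demonstrate a MCID reduction of 18% in NRS at the 1% significance level".

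The same paragraph reports feasibility figures of 67% good adherence and 73% NRS recording. It sets recruitment at 297 and makes 66 per group the target for the Per Protocol Set.

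The analysis is described differently.

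- Outcome measures: "The primary endpoint for this study is the proportion of participants experiencing this MCID improvement in each group".
- Statistical analysis and sample size: "The proportion of successes will be compared between groups (pairwise", by chi-squared or an exact test.
- The two comparisons with usual care are run "using 2.5% significance each". SHAPES versus TENS follows if at least one of them is significant.
- The analysis population is intention to treat.

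**The concern.** The calculation and the primary analysis differ in test (t-test against chi-squared), in endpoint scale (mean against proportion) and in significance level (1% against 2.5%). They also differ in population, because 66 is a per-protocol target while the analysis is by intention to treat. This is a conflict between two things the article states, not a detail it leaves to a fuller document.

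Reducing a continuous change to success or failure discards information, so a sample that gives 90% power on means will generally give less on responders for the same underlying effect. The Discussion presents the trial as a powered study able to give definitive evidence. A reader who takes 90% at face value could read a non-significant responder comparison as stronger evidence of no effect than it is. This matters most for SHAPES versus TENS, a primary objective for which no separate power is given.

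**Working it through.** **Inputs from the article.** 66 per group, 90% power, 1% level, t-test on means; primary test chi-squared at 2.5%; 297 randomised 1:1:1, so 99 per arm; 67% adherence; 73% NRS recording.

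**Inputs assumed.** Two-sided tests; normally distributed change with equal SD in both arms; control responder rate p0 from 10% to 50%. The article gives no SD and no responder rate.

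**1. The plan's own figures.** Without an SD, 66 cannot be reproduced independently, only inverted. By normal approximation, d = √(2/66) × (z for two-sided 1% + z for 90% power) = 0.671. The exact t-test solution is d = 0.680. That corresponds to an SD of 2/0.680 = 2.94 if the MCID is 2 points, or 1.8/0.680 = 2.65 if it is 1.8 points. The inflation does reproduce: 66/0.67 = 98.5, so 99 per arm and 297 in total.

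**2. Effect of alpha alone.** A t-test with d = 0.680 and 66 per arm has 90% power at 1% and 94.8% at 2.5%. The alpha mismatch is therefore conservative.

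**3. Effect of dichotomising.** Move the same shift to the responder scale with p1 = Φ(Φ⁻¹(p0) + 0.680). Then enumerate all outcome pairs and sum the probability that the uncorrected chi-squared test rejects at two-sided 2.5%. The 72 per arm is 0.73 × 99. In the diluted column the device rate is 0.67·p1 + 0.33·p0, which assumes that non-adherers respond at the control rate.

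| p0 | p1 | 66 per arm | 72 per arm | 99 per arm | 99 per arm, diluted |
|---|---|---|---|---|---|
| 10% | 27% | 65% | 68% | 83% | 51% |
| 20% | 44% | 77% | 80% | 92% | 60% |
| 30% | 56% | 81% | 83% | 94% | 62% |
| 40% | 67% | 82% | 84% | 94% | 62% |
| 50% | 75% | 79% | 82% | 93% | 57% |

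No control rate tried reaches 90% at 66 or 72 per arm. At 99 per arm, with every participant evaluable and the full effect, all but the 10% case do.

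**4. Detectable difference for 90% power at 2.5%** (normal approximation, control rates 20%, 30%, 40%): 28.6, 30.0 and 30.0 points at 66 per arm; 23.0, 24.5 and 24.7 points at 99 per arm.

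**5. SHAPES versus TENS, illustration only.** With 40% against 55% responding, which is an assumption, power at 66 per arm is about 32% at 2.5% and 39% at 5%. At 99 per arm it is 46% and 58%.

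**The case against.** A reader might go further and conclude that the trial does not have 90% power. The article does not support that. With no SD or responder rates the true power is unknown, and 66 is the per-protocol target while 99 per arm are randomised. On the same model, 99 evaluable participants per arm with an undiluted effect give 83–94%. This stands, and it is why the result must be shown across the number analysed. It does not rescue the stated figure, because the article attaches 90% to 66. The favourable case also needs complete NRS data and full adherence, where the feasibility study found 73% and 67%.

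A reader might also count the 1% level as a cause of lost power. It is not, since testing at 2.5% raises power. The level is only a mismatch, as no stated primary test uses 1%.

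It is equally tempting to say that the trial is badly underpowered for SHAPES versus TENS, or that a full MCID was assumed between those two arms. The article does not say which pair the calculation addresses, and 40% against 55% is not its figure. What stands is that power for this primary objective is not stated separately.

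Finally, the article says the calculation used simulations in R, and a condensed article need not list every input. But it names the test as a t-test for equal means, so the conflict with the chi-squared analysis is in its own text. No stated arithmetic is shown to be wrong.

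**Conclusion.** The point holds as a mismatch between sizing and analysis: the article's 90% power is not the power of its primary test, and nothing in it supports 90% for that test. At the 66 per group to which the claim is attached, the implied effect gives about 65–82%, a shortfall of roughly 8 to 25 percentage points. Whether the trial as run falls short depends on the number analysed under intention to treat and on dilution from non-adherence. Across the cases examined, power runs from about 51% to 94%.

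These figures rest on a two-sided reading, a back-solved d of 0.68, a normal shift with equal SD, assumed control rates of 10–50% and, for the lowest range, no benefit in non-adherers.

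**What to change.** Replace the power statement under Statistical analysis and sample size, and its duplicate under Participants, with one for the primary test. It should cover the chi-squared comparison of responder proportions at two-sided 2.5%, with the assumed usual-care and device responder rates and the number expected to be analysed under intention to treat. If responder rates cannot be justified, give the detectable difference instead: for 90% power and control rates of 20–40%, about 29–30 points at 66 per arm and 23–25 points at 99 per arm. If the t-test calculation is kept as history, label it as such and say that its 1% level is not the level of any primary test.

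State power for SHAPES versus TENS separately, at the alpha that comparison will receive from the gatekeeping procedure.

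The cost is one rewritten paragraph in two places and, probably, a less favourable stated power. The endpoint, test, alpha split and recruitment target stay as they are, and no patients are added.

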**Methods and design:**

Overall, 297 people with PSES will be randomised (1:1:1) to one of 3 arms: Standard care (no electrical stimulation), TENS (conventional patterned electrical stimulation) or SHAPES (adaptive patterned electrical stimulation). Both SHAPES and TENS are delivered using a specially designed electrical stimulation sleeve used for 60 min each day for 6-weeks. Outcome measures are completed at baseline, end of treatment (EOT 6 weeks) and then 6-weeks, 12-weeks and 24-weeks after the end of treatment. Efficacy will be determined based on the proportion of participants experiencing meaningful improvement (18%) in the 7-day Numerical Rating Scale (NRS-S) for PSES, compared between both intervention arms and standard care, and between the two intervention groups. Measures of arm motor function (Action Research Arm Test, MRC scale), and quality of life (SQoL-6D, EQ-5D) will also be measured along with a parallel health economic evaluation.

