### Participants

We calculated the sample size using data from our previous study [15]. The sample size calculation for a two group t-test for equal means showed that to conduct a three arm randomized control trial of SHAPES, TENS and ‘usual care’ control, we would need 66 subjects per group (total 198 participants) to have 90% power to demonstrate a MCID reduction of 18% in NRS at the 1% significance level to allow for multiple testing. In our feasibility study 67% of participants showed good adherence with the intervention and 73% with recording of NRS. We will recruit a total of 297 patients with PSES to the study who are being randomised to one of the 3 arms. We aim to achieve a minimum of sixty-six (66) participants to adhere to and complete the protocol in each group with good adherence to the intervention schedule and a minimum of 4 of 7 daily NRS-S recording.

Patients will be eligible to participate according to the inclusion and exclusion criteria listed in Table 1. Patients must be between 2 and 26 weeks from the onset of stroke and have any degree of arm spasticity (MAS ≥ 1) with at least mild weakness of the elbow flexors (MRC ≤ 4). Those with implantable electrical stimulation devices, participating in other interventional upper limb studies, or with pre-existing musculoskeletal of neurological disorders affecting elbow movement or spasticity are excluded. Aphasia and cognitive impairment are not exclusion criteria as long as patients can understand the intervention and complete study outcome measures.

Potentially eligible participants are identified by treating clinicians working in the stroke and rehabilitation services at Sheffield, Rotherham and Doncaster. Treating clinicians provide potential participants with the study information and obtain their consent to contact. Central researchers at Sheffield will call those consenting to be contacted via telephone to arrange a screening visit if they are willing to participate.

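### The total of 297 allows only for 67% adherence, not the 73% diary rate that the Per Protocol Set also needs, and the 90% power rests on that per-protocol count while the analysis is intention to treat

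*Protocol article*

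**What the plan says.** The sample-size text appears twice in the protocol article, under Participants and under Statistical analysis and sample size. It gives the base size: "we would need 66 subjects per group (total 198 participants) to have 90% power". The feasibility rates follow: "In our feasibility study 67% of participants showed good adherence with the intervention and 73% with recording of NRS". The recruitment figure is next: "We will recruit a total of 297 patients with PSES to the study who are being randomised to one of the 3 arms". The abstract gives the allocation ratio as 1:1:1, so 99 per arm.

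The target is then expressed as a per-protocol count: "We aim to achieve a minimum of 66 participants to adhere to and complete the protocol in each group". Membership of the Per Protocol Set requires both "good adherence to the intervention schedule and a minimum of 4 of 7 daily NRS-S recording".

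Statistical analysis and sample size opens with the analysis population: "Study analysis will be conducted on an intention to treat basis". The same section tests each device arm against usual care at 2.5%, whereas the sample size is stated as "90% power to demonstrate a MCID reduction of 18% in NRS at the 1% significance level to allow for multiple testing". The text on the interventions says that usual care participants get no device.

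**The concern.** Two separate losses are quoted, and the target population must survive both, but the inflation from 198 to 297 looks like an allowance for one. If so, the device arms may hold far fewer per-protocol participants than the number on which the power statement rests.

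There is also a mismatch of populations. The 90% is attached to 66 adherent participants with usable diaries in each group. The declared analysis keeps everyone as randomised, including the roughly one third of device participants expected not to adhere, and some of those analysed may have no valid 7-day NRS-S. A power figure for adherers does not carry over to that comparison. The Discussion presents the trial as a powered study giving definitive evidence, so a null result could be read as stronger evidence of no effect than the design supports.

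**Working it through.** **Inputs from the protocol article.** Target 66 per group; 90% power; 1% level; adherence 0.67; diary recording 0.73; total 297 at 1:1:1, so 99 per arm. Not given: the joint rate of the two conditions, the standard deviation behind the 66, and the sidedness of the test.

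**Step 1: reproduce 297.**
- Adherence only: 66/0.67 = 98.5, rounded up to 99; 3 × 99 = 297. Exact match.
- Diary only: 66/0.73 = 90.4, rounded up to 91; 3 × 91 = 273.
- Both, if independent: 0.67 × 0.73 = 0.489; 66/0.489 rounds up to 135; 3 × 135 = 405.

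The adherence rate alone explains the total.

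**Step 2: expected per-protocol number in a device arm of 99.** The joint rate lies between 0.67 + 0.73 − 1 = 0.40 and min(0.67, 0.73) = 0.67. Reaching 66 of 99 needs a joint rate of 66/99 = 0.667, practically the upper limit.

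| Overlap of the two failures | Joint rate | Expected of 99 | P(at least 66), binomial |
|---|---|---|---|
| All diary failures are non-adherers | 0.67 | 66.3 | 0.57 |
| Independent | 0.489 | 48.4 | 0.0003 |
| Least overlap | 0.40 | 39.6 | below 0.0001 |

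In the most favourable row, the chance that both device arms reach 66 is 0.575² = 0.33.

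**Step 3: usual care.** Only the diary condition can apply: 99 × 0.73 = 72.3, with P(at least 66) = 0.93. This arm is not short.

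**Step 4: power under intention to treat.** A two-sided two-sample t-test at 1% with 66 per group and 90% power implies a standardised difference d of about 0.68. This is back-solved, and two-sidedness is assumed. If the 33% non-adherers gain nothing (assumption), the as-randomised difference is 0.67 × 0.68 = 0.46, with the standard deviation left unchanged.

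| Analysed per arm | 1% level | 2.5% level |
|---|---|---|
| 99 (all give data) | about 73% | about 83% |
| 72 (99 × 0.73 with diary data) | about 55% | about 68% |

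The 1% column is the level in the sample-size statement; the 2.5% column is the level planned for each device arm against usual care. The 72-per-arm row assumes that 67% of those with diary data are adherent, as under independence.

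**The case against.** The strongest reply is that the shortfall is not proven. The joint rate is not in the document, and people who stop using the device may well be those who stop the diary. With complete overlap the expected count is 66.3, so 297 is arithmetically consistent with the aim. A reader might infer that 297 cannot deliver 66, or that the protocol breaks a promise. Neither is supported: the upper end of the range meets the target, and the text states an aim. A reader might also infer that all three arms fall short; usual care does not. What stands is that the aim needs the single best case and has no margin even then.

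The two rates are imprecise. The Introduction says that the feasibility trial randomised 16 patients. If the denominators were about 15 (an assumption: 10/15 and 11/15), exact 95% intervals are about 38–88% and 45–92%. Diary completion may also be better here: a 7-day baseline diary is described before randomisation, participants choose app or paper, everyone is contacted at 2–3 weeks, and the scale was adapted for aphasia and cognitive impairment. This is fair, and the tail probabilities show consistency with the quoted rates rather than forecast the trial. But these are the rates that the protocol itself uses for planning.

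On power, two replies have force. First, the 1% level is harsher than the planned 2.5%. With 48 against 72 at 2.5% and the undiluted d of 0.68, power against usual care stays just over 90%, so the per-protocol shortfall alone does not ruin that comparison. Second, zero benefit in every non-adherer is a strong assumption. If they gained half the effect, d would be 0.68 × (0.67 + 0.33 × 0.5) = 0.57, and power with all 99 analysed would be about 92% at 1%. If instead all diary failures were non-adherers, 66.3/72.3 = 92% of those with data would be adherent; d would be 0.68 × 0.92 = 0.62, and power with 72 per arm about 87% at 1%. The document does not say whether its 18% target is an as-randomised effect or an effect in adherers. These replies change the size of the loss. They do not make the stated 90% a figure for the declared analysis.

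Finally, a reader might infer that the trial will set selected device users against unselected controls and so lose the protection of randomisation. The document names a Per Protocol Set and sensitivity analyses for non-compliance, but describes no per-protocol contrast with usual care. How the set is defined in that arm belongs to an analysis plan that is not shown, so this is not part of the point.

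**Conclusion.** Wrong as written. The size of 297 follows from the 67% rate alone, although the set that it is meant to fill needs the diary condition as well. In the two device arms, the quoted rates give 40 to 66 per-protocol participants, about 48 under independence; only complete overlap supports 66. Usual care expects about 72. This range rests on the document's two rates alone; the value within it depends on the unreported overlap.

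The 90% power is tied to that per-protocol count and is not shown for the intention-to-treat analysis. The figures of 73% and 55% (1% level), or 83% and 68% (2.5% level), rest on d = 0.68 back-solved without a stated standard deviation, on no benefit in non-adherers, and, for the 72-per-arm figures, on adherence being unrelated to diary completion. They illustrate the possible loss for a comparison of means. The planned primary test compares proportions, and since the article gives no expected success rates, its power cannot be derived from the document.

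**What to change.** - Report, from the feasibility data, the proportion of participants who met both conditions (adherence and diary).
- Replace the statement of 66 in each group with the expected per-protocol number by arm: device arms 40–66, about 48 if the conditions are independent; usual care about 72. Once the joint rate is known, the device-arm range becomes one figure with its uncertainty.
- Restate power for the intention-to-treat comparison at the planned significance level, with explicit assumptions for the effect in non-adherers and for the number with a valid NRS-S. Say whether the 18% target is meant for all randomised participants or for adherers.

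The cost is a change of text and a short calculation on data already held. No extra patients are needed. The downside is that the stated figures become less favourable.
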